## STUDY SYNOPSIS

|                                        |                                                                                                                                                                                                                                                                                                                                                                                                                                                                                                                                                                                                                                                                                                                                                                                                                                                                                                                                                                                    |
|----------------------------------------|------------------------------------------------------------------------------------------------------------------------------------------------------------------------------------------------------------------------------------------------------------------------------------------------------------------------------------------------------------------------------------------------------------------------------------------------------------------------------------------------------------------------------------------------------------------------------------------------------------------------------------------------------------------------------------------------------------------------------------------------------------------------------------------------------------------------------------------------------------------------------------------------------------------------------------------------------------------------------------|
| Sponsor / Sponsor-Investigator: | Centre Hospitalier Universitaire Vaudois (CHUV) - [name], MD
( investigator-initiated trial )                                                                                                                                                                                                                                                                                                                                                                                                                                                                                                                                                                                                                                                                                                                                                                                                                                                              |
| Study Title:                    | Impact on clinical outcome of continuous video-encephalography (cEEG) monitoring in patients with disorders of consciousness: a randomized controlled trial                                                                                                                                                                                                                                                                                                                                                                                                                                                                                                                                                                                                                                                                                                                                                                                                                        |
| Short Title / Study ID:         | CERTA                                                                                                                                                                                                                                                                                                                                                                                                                                                                                                                                                                                                                                                                                                                                                                                                                                                                                                                                                                              |
| Protocol Version and Date:      | V2.0 dated 29.05.2017                                                                                                                                                                                                                                                                                                                                                                                                                                                                                                                                                                                                                                                                                                                                                                                                                                                                                                                                                              |
| Trial registration:             | www.clinicaltrial.gov Nr. NCT03129438
Federal Office of Public Health's (FOPH) portal Nr. tbd                                                                                                                                                                                                                                                                                                                                                                                                                                                                                                                                                                                                                                                                                                                                                                                                                                                                            |
| Study category and Rationale    | Risk category A, as:
-The health-related intervention investigated entails only minimal risks and burdens
-The health-related intervention investigated is recommended by the European Society of Intensive Care Medicine and the American Clinical Neurophysiology Society for most patients with consciousness disorders.                                                                                                                                                                                                                                                                                                                                                                                                                                                                                                                                                                                                                                                  |
| Clinical Phase:                 | NA                                                                                                                                                                                                                                                                                                                                                                                                                                                                                                                                                                                                                                                                                                                                                                                                                                                                                                                                                                                 |
| Background and Rationale:       | Continuous video-electroencephalography monitoring (cEEG), a non-invasive tool to monitor electrical brain function, improves seizure detection in comatose patients in intensive care units (ICUs). It is thus recommended for most patients with acute consciousness disorders. cEEG is however resource consuming compared to routine video-EEG (rEEG, lasting 20-30 minutes). While US centers have been using cEEG increasingly, all Swiss hospitals still do not have enough resources to comply with these guidelines. In addition, only one population-based study based on discharge diagnoses suggested that cEEG may improve patients' outcome. Current guidelines are thus based upon weak evidence and expert opinions: whether cEEG leads to improved patients' care remains elusive. Finally, little attention has been drawn towards quantitative EEG information beyond visual analysis, and the impact of such information on diagnosis, treatment, and outcome. |
| Objective(s):                   | To assess if cEEG in patients with consciousness impairment is related to better functional outcome as compared to rEEG, and to address the prognostic role of quantitative network EEG analyses in this cohort.                                                                                                                                                                                                                                                                                                                                                                                                                                                                                                                                                                                                                                                                                                                                                                   |
| Outcome(s):                     | Primary outcome: mortality at 6 months.
Secondary outcomes: functional outcome at 4 weeks and 6 months, seizure/status epilepticus (SE) detection rate and time to detection, infections rate, duration of intensive care unit stay, change in patient management (antiepileptic drug introduced, increased, or stopped, brain imaging), and costs.                                                                                                                                                                                                                                                                                                                                                                                                                                                                                                                                                                                                               |
| Study design:                   | Multicenter, open label, randomized, active controlled trial.                                                                                                                                                                                                                                                                                                                                                                                                                                                                                                                                                                                                                                                                                                                                                                                                                                                                                                                      |

|                                               |                                                                                                                                                                                                                                                                                                                                                                                                                                                                                                                                                                                                                                                                                                                                                                                                                                                                                                                                                                                                                                                                                                                                                         |
|-----------------------------------------------|---------------------------------------------------------------------------------------------------------------------------------------------------------------------------------------------------------------------------------------------------------------------------------------------------------------------------------------------------------------------------------------------------------------------------------------------------------------------------------------------------------------------------------------------------------------------------------------------------------------------------------------------------------------------------------------------------------------------------------------------------------------------------------------------------------------------------------------------------------------------------------------------------------------------------------------------------------------------------------------------------------------------------------------------------------------------------------------------------------------------------------------------------------|
| Inclusion / Exclusion criteria:        | 
Inclusion:
 
 
• In-patients aged <math>\geq 18</math> years, treated in an ICU or intermediate care unit.
 
• Alteration of mental state of any etiology (i.e., primarily cerebral or not), with Glasgow-coma scale <math>\leq 11</math> or FOUR score <math>\leq 12</math>.
 
• Need of an EEG to exclude seizures or SE, or to evaluate prognosis as per the treating physician or the consulting neurologist.
 
• Informed consent obtained for research in emergency situation according to Human Research Act (HRA) art 30-31 at the time of inclusion.
 
 
Exclusion:
 
 
• Clinical and/or electrographic status epilepticus < 96h before randomization
 
• Clinical and/or electrographic seizure < 36h before randomization
 
• Palliative care situation, in which detection of SE or seizures would not have any impact on the patient's care.
 
• High likelihood of needing a surgical intervention or invasive diagnostic procedure within the next 48 hours.
 
 |
| Measurements and procedures:           | 
Eligible patients will receive cEEG or rEEG in the first 48 hours following 1:1 randomization.
 
Demographics, etiology, Charlson Comorbidity Index, diagnosis leading to EEG, need and length of mechanical ventilation, and subsequent use of rEEG/cEEG will be prospectively collected. Outcomes will be assessed at 4 weeks and 6 months.
 
Analyses will compare the two interventional groups (intention to monitor, according to intervention allocation) regarding the outcomes. Additionally, lope cross correlation and horizontal visibility graphs will be applied to compute a weighted adjacency matrix consisting of pairwise interdependences between EEG signals, to characterize the integrative and segregative characteristics of the underlying functional brain networks and compare their relationship with the primary outcome.
                                                                                                                                                                                                                                                                                |
| Study Product / Intervention:          | Continuous video-EEG performed once for 30-48 hours.                                                                                                                                                                                                                                                                                                                                                                                                                                                                                                                                                                                                                                                                                                                                                                                                                                                                                                                                                                                                                                                                                                    |
| Control Intervention (if applicable):  | Routine video-EEG performed 2 times (20-30 min each) within 30-48 hours.                                                                                                                                                                                                                                                                                                                                                                                                                                                                                                                                                                                                                                                                                                                                                                                                                                                                                                                                                                                                                                                                                |
| Number of Participants with Rationale: | According to a previous estimate, patients with consciousness disorders undergoing cEEG have a 75% survival rate; while patients without cEEG 61%. Using a power of 0.8, an $\alpha$ error of 0.05, and a 2-side approach, 2x174 patients would be needed to detect this significant difference in survival (primary outcome).                                                                                                                                                                                                                                                                                                                                                                                                                                                                                                                                                                                                                                                                                                                                                                                                                          |
| Study Duration:                        | 30 months                                                                                                                                                                                                                                                                                                                                                                                                                                                                                                                                                                                                                                                                                                                                                                                                                                                                                                                                                                                                                                                                                                                                               |
| Study Schedule:                        | Planned First Patient First Visit (FPFV): April 2017
Planned Last Patient Last Visit (LPLV): September 2019                                                                                                                                                                                                                                                                                                                                                                                                                                                                                                                                                                                                                                                                                                                                                                                                                                                                                                                                                                                                                                          |

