|                                    |                                                                                                                                                                                                                                                                                                                                                                                                                                                                                                                                                                                                                                                                                    |
|------------------------------------|------------------------------------------------------------------------------------------------------------------------------------------------------------------------------------------------------------------------------------------------------------------------------------------------------------------------------------------------------------------------------------------------------------------------------------------------------------------------------------------------------------------------------------------------------------------------------------------------------------------------------------------------------------------------------------|
| Statistical Considerations: | 
Patients with consciousness disorders undergoing cEEG have a 75% survival rate; while patients without cEEG 61%. Using a power of 0.8, an <math>\alpha</math> error of 0.05, and a 2-side approach, 2x174 patients would be needed to detect this significant difference in survival.
 
At study completion, the two interventional groups will be compared regarding survival at six months as “intention to monitor” (predefined analysis for the primary endpoint) and “per protocol”, adjusted for potential confounders (logistic regressions).
 
Analysis of each secondary endpoint will be also conducted using univariable and multivariable approaches.
 |

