### **5.2 Secondary Outcomes**

- Functional outcome at four weeks and at six months (evaluated using the modified Rankin Scale (mRS), and the Cerebral Performance Categories (CPC) , ordinal),
- Evaluation at 4 weeks and 6 months of the ability to go back to work/school if previously working/at school (proportion),
- Seizure/SE detection rate, and time to detection after the start of EEG recording, and presence of concomitant clinical signs of seizures (proportion, resp. continuous variable)
- Detection of interictal potentially epileptiform features (spikes, spike and waves, sharp waves, isolated or repeated at <3Hz without any evolution; lateralized rhythmic delta activity  (proportion),
- Rate of in-hospital infections requiring antibiotic treatment at 4 weeks after first EEG (proportion),
- Need and duration of mechanical ventilation at 4 weeks after first EEG (proportion, resp. continuous variable),
- Duration if ICU and hospital stay (continuous variable),
- Patient destination after acute facility (home, rehab, nursing home, other; categorical)
- Change in clinical patient management (i.e., antiepileptic drugs (AED) introduced or stopped, AED increased or decreased, brain imaging procedure order) occurring during the 60 hours following the start of the first EEG (categorical).
- Correlation between quantitative EEG analysis and outcome.

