| SAEs potentially related to EEGs                                                      |                       | X            | X  |          |                 |                   |
| Changes in clinical management (treatment or new imaging)                             |                       |                     | X  |          |                 |                   |
| Last brain imaging results between 1 week before and 1 week after randomization       |                       |                     |           |          | X        |                   |
| Cerebral Performance Categories (CPC)                                                 |                       |                     |           |          | X        | X          |
| In-hospital infection requiring antibiotics                                           |                       |                     |           |          | X        |                   |
| Use of EEG after intervention                                                         |                       |                     |           |          | X        |                   |
| Need of mechanical ventilation                                                        |                       |                     |           |          | X        |                   |
| Discharge details (date, destination, back to work/school)                            |                       |                     |           |          | X        | X          |

[figure not shown]

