### 11.4 Planned Analyses

#### Analysis of the outcomes

All analyses will be carried out by a professional statistician. At study completion, the two interventional groups will be compared regarding survival at six months as "intention to monitor" (predefined analysis for the primary endpoint) and "per protocol", adjusted for potential confounders (logistic regressions).

Analysis of each secondary endpoint will be also conducted using univariate and multivariate approaches.

For univariate approaches, frequency tables ( $\chi^2$  or Fisher exact tests, as needed), t-test, Mann-Whitney U, and Kaplan-Meier tests will be applied, as needed.

For the multivariate approaches, stepwise logistic regression models will be performed to identify independent outcome predictors among those found to have a  $p < 0.1$  on univariate analyses. Accordingly, risk-prediction models will be set-up and "Goodness-of-fit" of these models will be evaluated using a Hosmer-Lemeshow test to ensure the quality of calibration. Solid predictors will be used to predict survival and functional outcome at six months in a model. To evaluate the performance of these models, sensitivity, specificity, positive predictive value, negative predictive value, unweighted accuracy (using exact binomial 95% CI), area under the Receiver Operating Characteristic (ROC) curve, and reclassification analysis (Net Reclassification Improvement – NRI) will be calculated .

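### Section 11.4 adjusts the randomised survival comparison for undefined confounders, and its only model-building rule (stepwise, univariate p < 0.1) does not exclude variables measured after allocation

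*Protocol*

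**What the plan says.** Section 11.4 (Analysis of the outcomes) and the synopsis (Statistical Considerations) compare the arms on six-month survival, by intention to monitor and per protocol, "adjusted for potential confounders (logistic regressions". The confounders are not named, and nothing says they must be recorded before randomisation.

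Section 11.4 continues: "Analysis of each secondary endpoint will be also conducted using univariate and multivariate approaches". It then says what the multivariable approach is: "stepwise logistic regression models will be performed to identify independent outcome predictors among those found to have a" p-value below 0.1 on univariate analysis. The same paragraph carries the result over to survival: "Solid predictors will be used to predict survival and functional outcome at six months in a model". No other rule for choosing model variables is given.

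Two variables that arise after allocation are collected. The synopsis (Measurements and procedures) says that "need and length of mechanical ventilation, and subsequent use of rEEG/cEEG will be prospectively collected", in the same sentence as demographics, etiology and the Charlson index. Section 5.2 lists as a secondary outcome "Need and duration of mechanical ventilation at 4 weeks after first EEG". The flow chart in section 9.1 schedules "Use of EEG after intervention" at week 4.

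**The concern.** In a randomised comparison, baseline confounding is absent in expectation. Covariate adjustment serves to gain precision and to correct chance imbalance, and it does so safely when the covariates are fixed before randomisation. A variable that follows allocation is not a confounder of the arm effect. Conditioning on it removes any effect that runs through it, and can add bias through shared causes of that variable and death.

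Both variables are exposed to this problem. Section 3.1 expects cEEG to detect more seizures than rEEG, and section 7.4 takes patients with detected seizures out of the intervention for management by best practice. Later EEG use and length of ventilation could therefore plausibly differ by arm. Both also stop accruing at death, so each carries information about survival to week 4. A screen at p < 0.1 against survival tends to favour variables of that kind.

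At stake is the adjusted estimate for the primary endpoint, whose covariates could be chosen by the outcome data and could include consequences of the randomised procedure.

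**Working it through.** **1. The plan's own figure.** Inputs from section 11.2: survival 61% (rEEG) and 75% (cEEG), two-sided alpha 0.05, power 0.80. The mean proportion is (0.61 + 0.75)/2 = 0.68.

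n = [1.96·√(2·0.68·0.32) + 0.8416·√(0.61·0.39 + 0.75·0.25)]² / 0.14² = (1.2930 + 0.5489)² / 0.0196 = 173.1, rounded up to 174 per arm.

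This reproduces the stated 2x174; power at 174 per arm is 0.802. The planned unadjusted mortality odds ratio is (0.25/0.75)/(0.39/0.61) = 0.521. Nothing in this point changes the sample size.

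**2. The two variables set against the rule.**

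| Variable | When recorded | Role stated in the protocol | Barred from the stepwise pool? |
|---|---|---|---|
| Need and length of ventilation | Week 4 (9.1, 9.2.2) | Secondary outcome (4.3, 5.2) | No |
| EEG use after the intervention | Week 4 (9.1) | None stated | No |

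The rule in section 11.4 tests only the univariate p-value. It has no condition on timing, so neither variable is excluded if the rule is followed as written.

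**3. How far the odds ratio could move.** The protocol gives no figure for the link between either variable and arm or death, so the inputs here are assumptions. Take a binary post-allocation variable M and the model logit P(death) = a + b·arm + c·M. Fix overall mortality at 39% (rEEG) and 25% (cEEG), and solve for a and b. The adjusted odds ratio is exp(b).

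One case in full: M in 50% of rEEG and 30% of cEEG patients, with an odds ratio of 4 between M and death.
- rEEG: with x = exp(a), 0.5·x/(1+x) + 0.5·4x/(1+4x) = 0.39 gives 4.88x² + 1.1x − 0.78 = 0, so x = 0.3027.
- cEEG: with y = exp(a+b), 0.7·y/(1+y) + 0.3·4y/(1+4y) = 0.25 gives 3y² + 0.65y − 0.25 = 0, so y = 0.2000.
- Adjusted odds ratio: 0.2000/0.3027 = 0.661.

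The same method over the assumed range:

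| M in rEEG | M in cEEG | OR of M with death = 2 | OR of M with death = 4 |
|---|---|---|---|
| 50% | 50% | 0.513 | 0.488 |
| 50% | 40% | 0.550 | 0.565 |
| 50% | 30% | 0.592 | 0.661 |
| 40% | 50% | 0.478 | 0.420 |
| 30% | 50% | 0.444 | 0.360 |

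If M is unrelated to death, the odds ratio stays at 0.521 in every row. The first row moves a little although M is balanced between arms. That is the non-collapsibility of the odds ratio, not bias. Relative to that row, the estimate is attenuated when M is rarer under cEEG and exaggerated when it is commoner. The illustration does not model shared causes of M and death, or truncation by death.

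**The case against.** The strongest reply is that the protocol never says these variables enter a model. That is correct as far as it goes. The synopsis sentence describes what is collected, and the analysis sentence in the same cell says only "Analyses will compare the two interventional groups (intention to monitor, according to intervention allocation) regarding the outcomes". A reader might infer a covariate list from the position of ventilation and later EEG use beside etiology and the Charlson index, but the documents contain no such list.

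A reader might also infer that later EEG use, being no listed outcome, can only serve as a covariate. That does not follow. Body weight, laboratory values and medication during EEG are also collected without a declared role, and later EEG use could simply describe contamination between arms.

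The stepwise step can further be read as prognostic modelling alone. It follows the sentence on secondary endpoints, and it leads to calibration, ROC and reclassification measures. Read literally, the word confounders excludes consequences of allocation, and the adjustment may be meant chiefly for the per-protocol analysis. Naming covariates can also be left to a statistical analysis plan, which is not shown.

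These replies limit the point but do not remove it. The protocol does more than leave the covariates open: it states a selection rule driven by the outcome and without a timing limit. Because secondary endpoints are said to be analysed this way as well, the natural reading is that the primary endpoint is too. No separate rule is given for the arm comparison, and the prediction models explicitly cover six-month survival.

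**Conclusion.** The point holds as a defect in a stated rule. Section 11.4 permits, without requiring, that the adjusted survival comparison be conditioned on variables that follow allocation and are truncated by death. Whether this happens depends on how the analyst reads the section and on which variables pass the screen.

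It would go too far to say that part of the cEEG effect is adjusted away. The sign depends on how arm relates to the variable, and the illustrated odds ratios run from 0.36 to 0.66 around a planned 0.52. A specific loss of power is not supported either. Simulated power of 36% to 39%, for example, needs half of the 14-point difference to run through ventilation, with an assumed log-odds of 1.8 for death. Under those inputs cEEG would have to cut ventilation from 50% to roughly 32%, and nothing in the protocol suggests that. The range above likewise rests on assumed frequencies and associations.

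The rule should be corrected before analysis. The design, the sample size and the unadjusted comparison by allocation are unaffected, so this is a should-fix item and not a fatal one.

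**What to change.** In section 11.4 and in the synopsis (Statistical Considerations):

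- State that every adjusted arm comparison uses a pre-specified set of values recorded before randomisation, for example age, Charlson index, etiology and pre-admission mRS, plus center, with no selection by p-value. Center belongs in the set because section 6.2.1 stratifies randomisation by it.
- State that ventilation and EEG use after the intervention are reported by arm only and do not enter these models.
- Describe the stepwise and risk-prediction models as prognostic work, separate from the estimate of the cEEG effect. Which time limit to set on prognostic predictors is the team's choice and is not needed to resolve this point.

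The cost is a few sentences. The suggested covariates are already collected, and no new data, patients or visits are needed. The covariate set should be fixed before outcome data by arm are examined. That includes the interim look in section 11.4.4, which the sponsor-coordinating investigator's own team conducts.
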